## Design Plan

- 3 Data is collected from study subjects that are not randomly assigned to a treatment. This includes surveys, "natural experiments," and regression discontinuity designs.

We will employ a quasi-experimental design to test the effectiveness of the MROT. Given the logistical and political considerations of evaluating the real-world implementation and effectiveness of a SAMHSA-funded program, a randomized controlled trial (RCT) is infeasible. Because this study is explicitly linked to, but not in total control over, the rollout of the SAMHSA-funded intervention, the study design must accommodate the fact that the SSA will implement a highly complex set of activities and is dependent on uptake of the program by each hospital ED. This logistical constraint makes it impossible to randomize en bloc. Therefore, a quasi-experimental design that rigorously controls for sources of confounding and bias is preferable. We anticipate there will be six hospital EDs in the implementation phase at the beginning of the study. Patients from these six hospitals who present with opioid overdose or a primary or secondary diagnosis of Opioid Use Disorder (OUD) and have contact with the MROT will be the intervention participants. Patients who present with these conditions at the hospitals that have not yet adopted the MROT program will serve as the control participants. We will analyze the data using a traditional approach that controls for sources of confounding and bias, while adjusting for clustering within hospitals. Also, we will analyze the data using a Propensity Score Matching approach to mitigate bias and support our ability to make causal inferences. All patient data will be obtained as de-identified secondary data from our state partners.

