#### 4.1 Sample Size:

In 2017, the six participating hospitals reported a total of 308 opioid-related poisoning visits to the ED, representing 37% (308/829) of the total visits statewide. Those numbers are highly conservative, because they are restricted to a small set of ICD-10 billing codes (primary diagnosis of T40.0, T40.1, T40.2, T40.3, T40.4, and T40.6). Other research found that using only ICD-9/10 billing codes related to opioid poisoning results in low sensitivity (as low as 25%). Additionally, rates of opioid-related visits have increased significantly over the past several years in Nevada (+12% 2010-2015, and +22% 2014-2015). Therefore, we anticipate that the actual number of intervention participants will be significantly higher. Using the findings from the sensitivity analysis above, we estimate the possible number of opioid-related poisonings for the 6 intervention hospitals to be 1232. The upper bound of the possible number of participants is represented by the total set of opioid-related ED encounters, which was 2635 in the six intervention hospitals in 2017, representing 37% (2635/7125) of encounters statewide. We anticipate 5% of control patients will access MAT compared to 33% of intervention patients. We anticipate that 7-12% of control patients will experience a non-fatal overdose in the 9 months following their index overdose, and that will be reduced by around 47% among intervention participants. According to unpublished data from the SSA, we anticipate 10% of control participants will die of an overdose in the next year compared to 5% in intervention participants.

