## Analysis Plan

- 6 We hypothesize that in the 9 months following their index overdose, patients exposed to the MROT will: H1: be more likely to initiate MAT (Primary outcome) H2: have fewer non-fatal ODs (Primary outcome) H3: be retained in MAT longer (Secondary outcome) H4: be less likely to die of a subsequent OD (Secondary outcome) All analyses will be conducted using the intent-to-treat principle. Demographic and descriptive statistics will be calculated at baseline and at 9-months following the index overdose. The baseline characteristics and main outcomes between the intervention and control groups will be compared using the chi-square test and the two-sample t-test. To test the hypotheses with the dichotomous outcome (initiation of MAT) and the ordinal outcome (incidence of non-fatal OD) we will use generalized linear mixed effects models (SAS PROC GLIMMIX) and Bayesian hierarchical models (SAS PROC MCMC) to account for the complexity of non-normal outcomes and intricate cluster effects due to the interdependence of patients within hospitals. The sensitivity analysis for Bayesian hierarchical models will also be performed. For the time to treatment, retention in treatment, and death due to subsequent OD outcomes, we will apply marginal Cox models (SAS PROC PHREG) to estimate the main effect of intervention exposure and use the robust sandwich covariance matrix estimation approach to account for the intracluster dependence. Individual demographic information including age, race, sex, drug of choice (heroin vs. prescription opioids), insurance type (e.g., Medicaid vs. private), and location of residence (urban vs. rural) will be included in the mixed effects models and marginal Cox models to control for potential confounding effects. We will obtain records from the SSA for 9 months prior to the index overdose for all participants, to allow us to control for prior history of non-fatal overdose and MAT utilization. Other covariates at the hospital level will include location (e.g., Northern Nevada vs. Southern Nevada, rural vs. urban) and hospital type (e.g., regional, university, trauma center, etc.). In addition to the statistical approach described above, we will also employ a propensity score (PS) matching approach as a secondary analysis. PS matching is particularly well-suited to "natural experiments" in which assignment to condition cannot be manipulated, such as the implementation of state programs. The approach involves calculating the probability of assignment to a treatment or exposure using logistic regression in which we enter observed characteristics that could influence assignment. In this case, known characteristics of patients such as age, sex, location of residence (rural vs. urban), previous history of overdose, or previous history of MAT enrollment. The PS reduces the large set of possible covariates that could influence selection into the intervention or control

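### Control status depends on when a hospital adopts MROT, but the protocol sets no rule for later adopters, no concurrency requirement and no calendar-time adjustment

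*Protocol*

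**What the plan says.** Section 3 (Design Plan) describes a non-randomised comparison. On the intervention side, "We anticipate there will be six hospital EDs in the implementation phase at the beginning of the study", and the intervention participants are described as "Patients from these six hospitals who present with opioid overdose" or opioid use disorder and have MROT contact. On the control side, patients at "hospitals that have not yet adopted the MROT program will serve as the control participants". The same section says that the study does not fully control the rollout, which "is dependent on uptake of the program by each hospital ED".

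Section 6 (Analysis Plan) lists the adjustment set:

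- Patient level: "Individual demographic information including age, race, sex, drug of choice (heroin vs. prescription opioids), insurance type" and urban or rural residence. These "will be included in the mixed effects models and marginal Cox models to control for potential confounding effects".
- History: overdose and MAT use in the 9 months before the index overdose.
- Hospital level: location and hospital type.
- Propensity score, given as examples: age, sex, residence, prior overdose and prior MAT enrolment.

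Index date, calendar period and time since launch appear nowhere. Section 4.1 states that "rates of opioid-related visits have increased significantly over the past several years in Nevada", giving +12% for 2010-2015 and +22% for 2014-2015. Section 5 notes an overdose-reporting law in force from July 1, 2017. Section 4.3 describes continual data collection. No accrual dates are given for either group.

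**The concern.** A control defined by not having adopted yet is defined partly by time. When a control hospital takes up MROT, it may leave the control pool, stay in it, or begin to supply intervention patients, and the protocol does not say which. If it leaves or switches, control index visits fall earlier on average than MROT index visits. The same happens if control visits are drawn from before MROT operation began, which nothing in the text excludes.

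Any change over time in the outcomes would then be attributed to MROT. The direction depends on the outcome. With later MROT patients, rising overdose risk or fuller reporting works against MROT on non-fatal overdose, while widening access to MAT works in its favour on MAT initiation. Hospital random effects and sandwich variances deal with dependence within hospitals, not with period. Propensity matching without index date can pair patients from different periods.

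**Working it through.** The protocol gives no figure for calendar-time bias, so there is none to reproduce. Its planning numbers do show how the groups were pictured. Statewide 2017 visits are split as 829 − 308 = 521 controls, and both groups are scaled up by the quoted 25% sensitivity: 308/0.25 = 1232 and 521/0.25 = 2084. That is one year divided between the six hospitals and the rest, which is a parallel picture.

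**Inputs**

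- Visit growth (section 4.1): +22% over one year (2014-2015), and +12% over 2010-2015. Taken as five years, the latter is 1.12^(1/5) = 1.023, or about 2.3% per year.
- Planned non-fatal overdose (section 4.1): 7-12% in controls, reduced by about 47%, so a risk ratio of 0.53.
- Assumed, not in the protocol: MROT index visits fall 3 to 6 months later on average, and outcome risk per patient grows at the visit rate.

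**Spurious ratio** = (1 + g)^t, with g the annual growth and t the gap in years.

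| g per year | t = 0 | t = 0.25 | t = 0.5 |
|---|---|---|---|
| 2.3% | 1.000 | 1.006 | 1.011 |
| 22% | 1.000 | 1.051 | 1.105 |

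The range is about 1.01 to 1.10. With no gap the ratio is exactly 1 for any g.

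**Effect on the planned risk ratio.** 0.53 × 1.006 = 0.533 and 0.53 × 1.105 = 0.586, so a true 47% reduction would appear as roughly 41% to 47%.

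**False-positive rate with no true effect.** This is a two-sided 5% two-proportion test, normal approximation, clustering ignored. Control risk is p and MROT risk is p(1 + g)^t, with t = 0.5. The lower growth rate is entered as 12/5 = 2.4%, immaterially different from 2.3%.

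| p | g | 308 vs 521 | 1232 vs 2084 |
|---|---|---|---|
| 7% | 2.4% | 5.1% | 5.1% |
| 7% | 22% | 7.1% | 12.6% |
| 12% | 2.4% | 5.1% | 5.2% |
| 12% | 22% | 8.5% | 18.7% |

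Worked line for the last cell:

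- MROT risk is 0.12 × 1.105 = 0.1325, a difference of 0.0125.
- The null standard error is 0.01187, so the critical difference is 1.96 × 0.01187 = 0.0233.
- The standard error under the trend is 0.0120.
- The upper-tail probability beyond (0.0233 − 0.0125)/0.0120 = 0.89 is 0.186. The lower tail adds 0.001, giving 0.187.

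**Is a 6-month gap attainable?** Section 4.3, read literally, ends the study 9 months after the first enrolment. If MROT patients accrue evenly over that window, their mean index date is 9/2 = 4.5 months. Controls from the same window cannot average earlier than month 0, so the gap stays below 4.5 months. A 6-month gap would need control visits from before MROT enrolment, or MROT accrual weighted to the end.

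**The case against.** The strongest reply is that the design as written is close to parallel. Six EDs are implementing from the start, intervention patients are tied to those six, and no later adopter, pre-period or historical control is described. A statewide trend then acts equally on both groups and no bias arises. This stands. A reader might infer from the control definition that secular trend is already confounded with exposure, but the documents do not support that. They leave staggered adoption possible; they do not say it will occur.

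The trend figures are also weak support. A reader might take both as annual rates of 12% and 22%, but the 12% spans 2010-2015. Both describe visit rates, cited to argue for a larger sample, and neither is a trend in repeat overdose or MAT initiation per patient. The reporting law is statewide, and without accrual dates nothing shows that index visits straddle its start. A change in MAT supply is plausible under a state grant but is not documented. For MAT initiation the planned contrast is 33% against 5%, a ratio of 6.6, beside which a 10% distortion is minor.

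Finally, the patient and propensity-score lists are worded as open, and an SAP could add terms. That softens the omission of calendar time. It does not settle which patients count as controls, which is a design matter that the protocol itself raises and leaves open.

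**Conclusion.** The point holds conditionally. The control definition depends on time, the rollout is outside the study's control, later adopters have no stated handling, concurrency is not required, and no named covariate is calendar time. If adoption is staggered or index dates differ between groups, the effect estimates are unprotected against trend; if accrual is fully parallel, a shared trend does no harm.

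The ratio of about 1.01 to 1.10 is an illustration. It rests on an assumed gap of 3 to 6 months, whose upper end is hard to reach under a literal reading of the stopping rule, and on visit growth standing in for outcome risk. At that size the bias would not overturn a true 47% reduction. At the larger planned sample and the upper growth rate, it could raise the false-positive rate well above 5%. Because protection is nearly free, the change is worth making before the data are analysed.

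**What to change.** 1. State how a control hospital that adopts MROT during the study is handled. Count its patients as controls only for index visits before its adoption date.
2. Restrict control patients to index dates concurrent with MROT operation.
3. Add calendar quarter of the index visit to every mixed, Bayesian and Cox outcome model and to the propensity score.

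The modelling cost is a few degrees of freedom: a 9-month window touches at most four calendar quarters, so three terms. Steps 1 and 2 may remove some control patients. The protocol does not say that visit dates are released in the de-identified extract, so index quarter should be requested from the state if it is not already supplied, along with each hospital's adoption status at the index visit.

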## Sampling Plan

- 4 Single state agency databases – Patient data from 3 databases maintained by the Nevada Department of Public and Behavioral Health will be linked at the state level, de-identified, and sent to the research team for quantitative analysis. The databases include: statewide hospitalization data, statewide mortality data, and statewide medication assisted treatment participant data, In person interviews with patients conducted after exposure to mobile outreach teams will be conducted by research assistants to assess team interaction,

demographics, and drug use behaviors and impact of the intervention on patients. In person interviews for feasibility and acceptability will be conducted in rural Nevada with emergency department staff and other applicable community members that may be utilized for mobile recovery activities.

#### 4.1 Sample Size:

In 2017, the six participating hospitals reported a total of 308 opioid-related poisoning visits to the ED, representing 37% (308/829) of the total visits statewide. Those numbers are highly conservative, because they are restricted to a small set of ICD-10 billing codes (primary diagnosis of T40.0, T40.1, T40.2, T40.3, T40.4, and T40.6). Other research found that using only ICD-9/10 billing codes related to opioid poisoning results in low sensitivity (as low as 25%). Additionally, rates of opioid-related visits have increased significantly over the past several years in Nevada (+12% 2010-2015, and +22% 2014-2015). Therefore, we anticipate that the actual number of intervention participants will be significantly higher. Using the findings from the sensitivity analysis above, we estimate the possible number of opioid-related poisonings for the 6 intervention hospitals to be 1232. The upper bound of the possible number of participants is represented by the total set of opioid-related ED encounters, which was 2635 in the six intervention hospitals in 2017, representing 37% (2635/7125) of encounters statewide. We anticipate 5% of control patients will access MAT compared to 33% of intervention patients. We anticipate that 7-12% of control patients will experience a non-fatal overdose in the 9 months following their index overdose, and that will be reduced by around 47% among intervention participants. According to unpublished data from the SSA, we anticipate 10% of control participants will die of an overdose in the next year compared to 5% in intervention participants.

#### 4.2 Sample Size Rationale:

The alpha significance level of the power analysis is set to 0.05. At least 82% power will be achieved to detect a small effect size of 0.2 under the anticipated conservative sample size. Under different assumptions of effect size, such as medium effect size of 0.5 and large effect size of 0.8, our analysis strategy will have at least 99% power. For reasonably anticipated sample size 3316 (1232 intervention and 2084 control), at least 99% power will be achieved to detect as small as 0.1 effect size. Therefore, a very conservative sample of 829 (308 intervention and 521 control) patients will be sufficient to evaluate the primary outcomes. R package pwr was used for power analysis. To be our best knowledge, very few existing power analysis approaches can be applied to hierarchical models. In addition to the primary aims of the proposal, data will be used to develop a statistically reliable and computationally efficient power analysis procedure for hierarchical models and implement the proposed approach in an R package and a SAS macro.

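### The 829-patient planning sample takes ED visits as patients and assumes every intervention visit leads to MROT contact, so it is not a demonstrated floor for power

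*Protocol*

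**What the plan says.** Protocol section 4.1 reports that in 2017 "the six participating hospitals reported a total of 308 opioid-related poisoning visits to the ED, representing 37% (308/829) of the total visits statewide". It calls these counts conservative because they cover only a few primary-diagnosis T40 codes, because such coding may have sensitivity as low as 25%, and because visits have been rising. It multiplies 308 by four to reach 1232 and takes 2635 encounters as an upper bound on participants.

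Section 4.2 then reuses the first pair of counts with a different unit: "a very conservative sample of 829 (308 intervention and 521 control) patients will be sufficient to evaluate the primary outcomes". It claims at least 82% power for an effect size of 0.2 at that size.

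The Design Plan (section 3) defines the arms. Patients at the six hospitals who present with overdose or OUD "and have contact with the MROT will be the intervention participants". Patients at "hospitals that have not yet adopted the MROT program will serve as the control participants". The Hypotheses and Analysis Plan sections say that all analyses follow intent-to-treat.

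**The concern.** Two steps are missing between the count and the sample size.

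- **Visits to patients.** The outcomes are per patient, measured from an index overdose. Section 4.1 expects 7–12% of control patients to overdose again within 9 months, and Measured Variables defines that outcome as an overdose treated by ED personnel, which is another ED visit. Some of the 829 visits are therefore likely to be repeats, and nothing removes them.
- **Presentation to contact.** The 308 is every coded poisoning visit at the six hospitals, but the arm is limited to patients the MROT reached. No contact share is applied to 308, 1232 or 2635, so full contact is assumed without being stated.

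Section 4.2 presents 829 as enough on its own for both primary outcomes. If it is not a true lower bound, that assurance is unsupported, and non-fatal overdose is the outcome most exposed.

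**Working it through.** **Inputs.** From the protocol: 308 and 521 (829 − 308); two-sided alpha 0.05; effect size 0.2; MAT initiation 5% vs 33%; non-fatal overdose 7–12% in controls with a 47% reduction; 1232/2084 as the larger scenario. Not in the protocol, so assumed: the share of visits that are unique patients, and the MROT contact share. Patients are treated as independent throughout, with no hospital clustering.

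**Formula.** For a standardised difference d, the noncentrality is δ = d × √(n₁n₂/(n₁+n₂)), and power comes from the noncentral t distribution with n₁+n₂−2 degrees of freedom.

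**1. The stated figure.** At 308/521: √(160,468/829) = 13.913, δ = 2.783, power 79.4%. With equal arms of 414.5: √207.25 = 14.396, δ = 2.879, power 82.0%. The 82% is matched by an equal split of 829, not by 308/521. This gap comes from allocation and exists before any correction for visits or contact.

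**2. Repeat visits only.** Two conversions of the 7–12% rate r:
- Unique share 1/(1+r): 0.935 to 0.893, giving 288/487 to 275/465 patients and power of about 77% to 75%.
- Constant monthly rate −ln(1−r)/9 over an average 6 remaining months of the year: 0.048 to 0.085 repeats per patient, unique share 0.954 to 0.921, 791 to 764 patients, power about 77% to 76%.

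**3. Contact only** (521 controls kept, assumed shares):

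| Contact share | Intervention n | δ | Power at 0.2 |
|---|---|---|---|
| 80% | 246 | 2.587 | 73% |
| 60% | 185 | 2.336 | 65% |
| 50% | 154 | 2.181 | 59% |

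If intent-to-treat instead means everyone presenting at an MROT hospital, n stays at 308 but the effect is diluted. Taking 0.2 as the effect among contacted patients and none in the rest, half contact gives d = 0.2 × 0.5 = 0.1, δ = 0.1 × 13.913 = 1.391 and power of about 28%.

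**4. The offset in the protocol.** Accept the fourfold under-count (1232/2084) and apply 25% contact. This leaves 308/2084: √(308 × 2084/2392) = 16.381, δ = 3.276, power 90.6%. Adding the 1/1.12 repeat correction gives 275/1861 and 87.2%. The intervention arm stays at 308 or more as long as unique share × contact share is at least 308/1232 = 0.25.

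**5. By primary outcome.** Cohen's h = 2·arcsin√p₁ − 2·arcsin√p₂, with z = h × √(n₁n₂/(n₁+n₂)) compared with 1.96.

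| Outcome | h | Power at 308/521 | Power at 154/521 |
|---|---|---|---|
| MAT initiation, 5% vs 33% | 0.773 | over 99% | over 99% |
| Non-fatal overdose, 12% vs 6.36% | 0.198 | about 78% | 58% |
| Non-fatal overdose, 7% vs 3.71% | 0.148 | 54% | 36% |

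A standard two-proportion formula is lower for non-fatal overdose: 76% and 50% at 308/521, 51% and 29% at 154/521. MAT initiation stays above 99% even with 77 intervention patients.

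**The case against.** The strongest reply is that section 4.1 gives a reason for calling the count conservative, and it works in the opposite direction. The 308 covers only primary T40 codes, sensitivity may be as low as 25%, visits are rising, and the Design Plan also admits patients with an OUD diagnosis who fall outside the 308. On the protocol's fourfold figure, even 25% contact keeps about 91% power at effect size 0.2. Section 4.3 adds that data collection continues regardless of the planned bounds, so 829 is a planning scenario rather than a recruitment target.

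This stands. A reader might infer that the sample and its power are overstated overall, or that the study is too small. The documents do not support that: the losses and the gains are both unquantified.

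Three further points have force. The contact shares are assumptions with no source in the protocol. The repeat-visit effect is small, and if poor coding sensitivity applies equally to repeat visits, fewer of them sit inside the 829, the unique share is about 98–99% and power stays at about 79%. The contact loss in n applies only on the Design Plan's definition of the arm, not under intent-to-treat by hospital.

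The reply still does not rescue the sufficiency claim. The 1232 is 308 × 4 and the 2635 are encounters, so both carry the same two omissions. Even at 1232/2084, 25% contact leaves only about 61% (two-proportion) to 68% (Cohen's h) power for non-fatal overdose at a 7% control rate.

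**Conclusion.** The relabelling of visits as patients and the unstated assumption of full contact are both plain in the text, and 829 is not a demonstrated floor. The figure of 82% is not delivered at the stated split (79.4%). Each omission taken alone lowers it further: to about 75–77% for repeats, and to 73%, 65% or 59% for assumed contact of 80%, 60% or 50%. Whether the eventual sample falls below or above 829 cannot be settled from the documents.

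The shortfall from 82% to 79.4% should not be read as an effect of visits or contact; it is due to unequal allocation.

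The practical risk lies with one primary outcome. MAT initiation is safe in every scenario tried. Non-fatal overdose, on the protocol's own rates, corresponds to effect sizes of 0.148 to 0.198, below the 0.2 used for planning. It has about 54–78% power at the full 308/521 and 36–58% at half contact. These figures assume independent patients and Cohen's h.

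**What to change.** 1. Recount the 2017 extract as unique patients at their first qualifying visit, for the six MROT hospitals and for the controls.
2. Reconcile the contact-based arm in the Design Plan with intent-to-treat in the Hypotheses and Analysis Plan sections. If the arm is contacted patients, state an assumed contact share with a range and apply it to the intervention n. If it is all patients at MROT hospitals, keep n and dilute the effect.
3. Recompute power at the actual unequal split, separately for MAT initiation and non-fatal overdose, using the rates in section 4.1. Recheck the 3316 line too: with four times the n and half the effect size, δ is again 2.783, so power as a standardised difference is 79.4%, not 99%.
4. Replace the statement that a very conservative 829 is sufficient for the primary outcomes with the restated figures, showing the coding offset as a separate, explicit assumption.

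The cost is one query on data the state already holds, and a rewrite of sections 4.1 and 4.2. No change to data collection is needed.

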#### 6.1 Inference Criteria:

A p-value of  $<0.05$  will be considered statistically significant. 95% Confidence Intervals will be reported and all hypothesis testing will be two-sided. All analyses will be performed using SAS Version 9.4 for Windows.

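### The stated 82% and 99% power come from independent-patient formulas although exposure is set by hospital, and the unadjusted chi-square and t-test comparisons of the main outcomes ignore clustering too

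*Protocol*

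**What the plan says.** The Design Plan takes intervention patients from hospitals that have adopted the programme ("We anticipate there will be six hospital EDs in the implementation phase at the beginning of the study") and controls from hospitals that have not. As described, no hospital supplies both arms. The number of control hospitals is not given.

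Section 4.2 claims, for its smaller sample and a 0.05 level: "At least 82% power will be achieved to detect a small effect size of 0.2 under the anticipated conservative sample size". For 3316 patients (1232 intervention, 2084 control) it claims at least 99% at effect 0.1. The tool is named: "R package pwr was used for power analysis". The section remarks that few power methods suit hierarchical models, leaves such a method to later work, and still concludes that "a very conservative sample of 829 (308 intervention and 521 control) patients will be sufficient to evaluate the primary outcomes".

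The Analysis Plan recognises dependence among patients of one hospital. It tests MAT initiation and non-fatal overdose with mixed and Bayesian hierarchical models. For the Cox outcomes it will "use the robust sandwich covariance matrix estimation approach to account for the intracluster dependence". The same section, and the Hypotheses section, also state: "The baseline characteristics and main outcomes between the intervention and control groups will be compared using the chi-square test and the two-sample t-test". Section 6.1 applies p<0.05 to the results without separating these comparisons from the models: "95% Confidence Intervals will be reported and all hypothesis testing will be two-sided".

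**The concern.** When a whole hospital is either exposed or not, the information about the effect depends on the number of hospitals as well as the number of patients. A formula for independent patients then gives too high a power for any positive ICC. The protocol accepts the dependence in its analysis but makes no allowance for it in its power, and then calls 829 patients enough for both primary outcomes. A null result on non-fatal overdose could be read as absence of effect when the study had little chance of finding one.

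The chi-square and t-test comparisons raise a second problem. They ignore clustering and, in a non-randomised design, confounding. Each primary outcome would have an unadjusted p-value beside a model-based one, and nothing says which governs under the 0.05 rule.

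**Working it through.** **Inputs from the protocol.** Two-sided alpha 0.05; 308 vs 521 and 1232 vs 2084 patients; six exposed hospitals. From section 4.1: MAT initiation 5% vs 33%; non-fatal overdose 7-12% in controls, reduced by about 47%, so 7% vs 3.71% or 12% vs 6.36%.

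**Assumptions, not in the protocol.** ICC 0.005 to 0.05; 6 to 30 control hospitals; equal hospital sizes within an arm; non-fatal overdose taken as any vs none, because section 4.1 gives a proportion.

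**1. The plan's own figures, independent patients.** Power = Φ(d/√(1/n₁+1/n₂) − 1.96).

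- d = 0.2, 308 vs 521: 0.2/√(1/308+1/521) = 2.783; Φ(0.823) = 79.5% (noncentral t 79.4%). An equal split, 414 vs 415, gives 82.0%. The stated 82% is therefore an independent-patient figure for equal groups, with no cluster allowance.
- d = 0.1, 1232 vs 2084: again 2.783 and 79.5%. Since 3316 = 4 × 829, half the effect with four times the patients leaves power unchanged. The 99% cannot stand on the same scale as the 82%. Reading 0.1 as the chi-square effect w gives over 99% at 3316, but then 0.2 at 829 also gives over 99%.
- Effects 0.5 and 0.8 at 829: over 99%, as stated.

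**2. With clustering.** Design effect per arm: DE = 1 + (n/k − 1) × ICC, where k is the number of hospitals. Var = DE₁/n₁ + DE₂/n₂; power = Φ(d/√Var − 1.96). The mean exposed hospital has 308/6 = 51.3 or 1232/6 = 205.3 patients.

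- Mildest case, 829 patients, ICC 0.005, 30 control hospitals: DE 1.252 and 1.082; Var = 1.252/308 + 1.082/521 = 0.00614; 0.2/0.0784 = 2.552; Φ(0.592) = 72.3%.
- Harshest case, ICC 0.05, 6 control hospitals: DE 3.517 and 5.292; Var = 0.02157; 0.2/0.1469 = 1.362; Φ(−0.598) = 27.5%.

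For non-fatal overdose the numerator is p₂ − p₁ and each arm's variance is p(1−p) × DE/n.

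Power in %, lowest to highest over 6-30 control hospitals:

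| ICC | d=0.2, N=829 | d=0.1, N=3316 | OD 7%, N=829 | OD 12%, N=829 | OD 7%, N=3316 | OD 12%, N=3316 |
|---|---|---|---|---|---|---|
| 0 | 79.5 | 79.5 | 56.3 | 80.9 | 98.9 | >99 |
| 0.005 | 67.9-72.3 | 45.2-55.2 | 44.8-50.2 | 68.6-74.7 | 78.3-90.7 | 95.6-99.2 |
| 0.01 | 58.6-66.0 | 31.3-41.5 | 37.1-45.2 | 58.8-69.1 | 58.7-79.2 | 83.1-95.9 |
| 0.02 | 45.5-55.6 | 20.1-28.0 | 27.9-37.7 | 45.3-59.5 | 38.0-59.9 | 60.1-83.8 |
| 0.05 | 27.5-37.4 | 11.3-15.5 | 17.0-25.6 | 27.0-41.4 | 19.4-33.3 | 31.2-53.1 |

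The overdose columns use the unpooled variance. A pooled variance under the null gives 50% and 76% in place of 56% and 81% at N=829 with ICC 0. MAT initiation exceeds 99% in every cell. A t reference on hospitals minus 2 degrees of freedom lowers power a little more: with 20 control hospitals and d=0.2 at N=829, from 72% to 68% at ICC 0.005 and from 36% to 33% at ICC 0.05.

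**3. The chi-square and t-test comparisons.** Let r = √[Var/(1/n₁+1/n₂)], the true standard error over the naive one. True type I error = 2[1 − Φ(1.96/r)].

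| ICC | N=829 | N=3316 |
|---|---|---|
| 0.005 | 7.2-8.8% | 14.1-19.5% |
| 0.01 | 9.5-12.5% | 21.9-30.0% |
| 0.02 | 13.9-19.3% | 33.2-42.9% |
| 0.05 | 24.9-33.8% | 50.6-59.8% |

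r runs from 1.09 to 2.04 at N=829 and from 1.33 to 3.72 at N=3316. The excess grows with the larger sample that the protocol expects.

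**The case against.** The strongest reply is that the hypothesis tests already handle clustering. That stands. A reader might infer that all the planned confidence intervals are too narrow. The documents do not support this: the Design Plan promises adjustment for clustering, and the Analysis Plan names GLIMMIX, Bayesian hierarchical and sandwich-variance Cox models. The type I error figures above concern only the chi-square and t-test comparisons. Those follow a sentence on descriptive statistics and may be meant as a summary, but the text calls them comparisons of main outcomes and section 6.1 does not exempt them.

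A reader might also infer that the Cox sandwich variance is uncorrected and so too small with six exposed hospitals. The protocol does not say whether a correction is used, and that detail can be left to the SAP.

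The ICC and control-hospital count are assumptions, and the lowest powers need the least favourable pair. Adjustment for hospital location and type and for prior overdose and MAT history could lower the residual ICC; unequal hospital sizes would push the other way. Section 4.2 discloses the difficulty with hierarchical power, but a disclosure without an allowance does not support the figures that follow it. Finally, section 4.3 collects every eligible patient whatever the planned size, so a restated power changes no enrolment. That limits the consequence to how results are read; it does not make the figures correct.

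**Conclusion.** The power statement in section 4.2 is wrong as written. Without clustering, the stated allocations give about 79%, not 82% or 99%. Under the assumed ICC and hospital counts, power is 72-28% (effect 0.2, N=829) and 55-11% (effect 0.1, N=3316). It would be wrong to blame clustering for the whole drop from 99%: the first 20 points or so are the separate arithmetic error.

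Nor is the study underpowered throughout. MAT initiation at the anticipated rates is safe. The sufficiency claim fails for non-fatal overdose at N=829 over the whole assumed range, and at a 7% control rate it fails even with independent patients (56%). At N=3316 that outcome has about 91-19% (7% rate) or 99-31% (12% rate), so it is adequate only at low ICC.

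The unadjusted outcome tests do not hold their nominal 5% level under any positive ICC. The size of the excess, roughly 7-34% or 14-60% by sample size, rests on the same assumptions.

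**What to change.** 1. In section 4.2, recompute power with a design effect (or by simulating the planned mixed model) over a stated ICC range, with the actual number of exposed and control hospitals, the stated allocation and the outcome rates of section 4.1. Correct the 82% and 99%, and qualify the sufficiency conclusion for non-fatal overdose.
2. In the Hypotheses and Analysis Plan sections, remove the chi-square and t-test p-values for the main outcomes or label them descriptive. State in section 6.1 that the cluster-adjusted models alone govern inference.

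The cost is protocol wording and a few lines of code. Enrolment and the planned models stay as they are. The downside is a lower stated power.
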